# Effects of Keluoxin capsule combined with losartan potassium on diabetic kidney disease: study protocol for a randomized double-blind placebo-controlled multicenter clinical trial

**DOI:** 10.1186/s13063-020-04852-8

**Published:** 2020-11-23

**Keywords:** Chinese medicine, Diabetic kidney disease, Protocol, Randomized controlled trial

## Abstract

**Background:**

Diabetic kidney disease (DKD) is one of the most important microvascular complications of diabetes, and its prevalence has increased dramatically in the past few decades. DKD is responsible for considerable morbidity and mortality of patients with diabetes. Keluoxin capsule (KLX) is a Chinese patent medicine that has been used in the clinic to control DKD for years. Previous studies have shown that KLX appears to reduce proteinuria, but the study protocols as well as the primary outcome need to be improved. Thus, we aim to evaluate whether losartan potassium combined with KLX is more effective than losartan potassium in DKD treatment and to provide validated evidence for the application of KLX in the treatment of DKD.

**Methods:**

We will conduct a randomized double-blind placebo-controlled multicenter clinical trial. A total of 252 participants diagnosed with DKD recruited from 18 institutions will be randomly allocated to either a losartan potassium plus KLX (*n* = 126) or a losartan potassium plus placebo group (*n* = 126). The participants will be administered KLX or placebo in addition to losartan potassium for 24 weeks. The primary outcome measure will be the decline in estimated glomerular filtration rate (eGFR) (ml/min/1.73 m^2^/year) from baseline within 24 weeks, and the secondary outcomes will be the incidence of serum creatinine doubling, the incidence of end-stage renal disease (ESRD), the proportion of subjects with a progressive decline in eGFR > 30%, the percent change in 24 h urinary total protein (UTP), the change in the urinary albumin/creatinine ratio (UACR), and the total effective rate of the traditional Chinese medicine (TCM) syndrome scale scores. Comparison of the differences in the variables between groups will be performed according to the data revealed by independent *t* tests, chi-squared tests, Fisher’s exact tests, or Wilcoxon’s tests. All statistical tests will be two-sided, and significance will be considered for *p* values < 0.05.

**Discussion:**

This study will be the first randomized clinical trial to evaluate the efficacy and safety of KLX versus the placebo for the treatment of patients with DKD. The outcome of this trial will provide a basis for prescribing KLX to patients with DKD.

**Trial registration:**

Chinese Clinical Trial Registry (www.chictr.org.cn) ChiCTR1900021113. Registered on January 29, 2019.

## Background

Diabetic kidney disease (DKD), a chronic progressive disorder that is characterized by proteinuria and an irreversible decline in renal function, ultimately leads to end-stage renal disease (ESRD) in approximately 50% of patients in developed countries [1, 2]. DKD is one of the most important microvascular complications of diabetes, and its prevalence has increased dramatically worldwide in the past few decades [3, 4]. DKD accounts for approximately 20% of new dialysis prescriptions [5], and the high medical cost of renal dialysis treatment has created an urgent need for additional therapeutic strategies for DKD [6]. Comprehensive measures such as hypoglycemic and antihypertensive treatments have demonstrated beneficial effects in preventing the development of DKD, especially when used at the stage of microalbuminuria, and angiotensin-converting enzyme inhibitors (ACEIs) and angiotensin receptor II blockers (ARBs) reduce the risk of progression of DKD [7–9]. Losartan potassium, a classic angiotensin receptor blocker, is helpful in protecting the kidneys from damage in DKD [10]. In addition, this drug was recommended on the list of essential medicines of World Health Organization, which included the most effective and safe medications that experts consider necessary in a healthcare system. Treatment with losartan potassium may preserve some features of kidney structure and microalbuminuria due to its action on attenuating kidney fibrosis [11, 12]. However, combinations of traditional Chinese medicine (TCM) and Western medicine have advantages over Western medicine in delaying the progression of CKD and improving quality of life.

Keluoxin capsule (KLX) is a Chinese patent drug developed by the Chengdu Kanghong Pharmaceutical Co., Ltd. and Guang’anmen Hospital of the China Academy of Chinese Medical Sciences. KLX consists of six natural herbs: *Astragalus membranaceus*, *Ligustrum lucidum*, leech, rhubarb, Radix Pseudostellariae, and the fruit of the Chinese wolfberry (https://www.cnkh.com/product/17156.htm). KLX is used for DKD in patients with syndromes of qi and yin deficiency and blood stasis because it nourishes qi and yin, promotes blood circulation, and removes blood stasis. KLX was once named Tangshenping or Tangweikang [13, 14]. Research on KLX for DKD is included in the national Ninth Five-Year Plan project.

KLX was placed on the market in 2009 (the approval number is National Medicine Standard Z20090035) and is considered a B category drug by Chinese medical insurance. Previous studies have shown that KLX can regulate glucose and lipid metabolism, improve renal hemodynamic parameters, and protect against pathological damage in diabetic rats [13]. KLX can also reduce high glomerular perfusion and filtration rates and thus delay the processes of glomerular fibrosis and hardening in diabetic nephropathy rat models [15]. In addition, KLX was approved for clinical trials by the State Food and Drug Administration in 2003. The results of the trials showed that KLX is effective in controlling 24 h urinary total protein (UTP) levels, urinary albumin (ALB)/creatinine ratios (UACRs), and TCM syndrome scale scores [13, 16]. Moreover, both acute toxicity tests and long-term toxicity tests have verified the safety KLX in the treatment of DKD.

However, there is a lack of validated evidence regarding the effectiveness of KLX in DKD. Previously, the efficacy evaluation of KLX is focused on urine protein, but the influence of KLX on kidney progression of DKD, which is assessed by a change from baseline in the eGFR, has not been previously assessed. Therefore, in the proposed study, we will conduct a randomized double-blind placebo-controlled multicenter clinical trial to evaluate whether KLX combined with losartan potassium tablets is more effective in delaying the progression of DKD than losartan potassium tablets based on the pathophysiological mechanism of the development of DKD.

## Methods/design

### Study objectives

The objective of this trial is to evaluate whether the effect of losartan potassium combined with KLX is superior to that of losartan potassium in DKD treatment and to obtain validated evidence for the application of KLX in the treatment of DKD.

### Study design

This will be a double-blind randomized controlled trial to investigate the efficacy of KLX combined with losartan potassium compared with a placebo. The study will be conducted in eighteen centers in China: Guang’anmen Hospital of the China Academy of Chinese Medical Sciences, Dongzhimen Hospital of Beijing University of Chinese Medicine, the First Affiliated Hospital of Chengdu Medical College, Mianyang Central Hospital, the Affiliated Hospital of Chengdu University of Traditional Chinese Medicine, Dazhou Central Hospital, Dezhou People’s Hospital, Linfen Central Hospital, the Affiliated Hospital of Liaoning University of Traditional Chinese Medicine, the First People’s Hospital of Luoyang, Shenzhen Hospital of Southern Medical University, Shanghai Shuguang Hospital, Yueyang Hospital of Integrated Traditional Chinese and Western Medicine, Shanghai University of Traditional Chinese Medicine, the Second Affiliated Hospital of Wannan Medical College, Nanyang City Central Hospital, the First Affiliated Hospital of Henan University of Chinese Medicine, Xinxiang Central Hospital, and Heze Municipal Hospital. Patients with DKD who want to participate in the study will undergo a standardized baseline evaluation before treatment including detailed history evaluation, physical examination, and laboratory testing. The enrolled participants will be randomly allocated to the losartan potassium plus KLX treatment or losartan potassium plus placebo control groups. The participants will be administered KLX or placebo in addition to losartan potassium for 24 weeks. Data will be collected during three visits to assess the efficacy of KLX and will be recorded on case report forms (CRFs). A flowchart of the study design is shown in Fig. 1, and the time points of assessment are shown in Table 1. The Standard Protocol Items: Recommendations for Interventional Trials (SPIRIT) guidelines [17] were followed during the development of the protocol of this study (Additional file 2).

**Fig. 1. Fig1:**
[figure not shown]
Trial flowchart

**Table 1 Tab1:**
[figure not shown]
Schedule of enrollment, intervention, and assessment

*Abbreviations*: *24 h UTP* 24 h urinary total protein, *UACR* urinary albumin/creatinine ratio, *eGFR* estimated glomerular filtration rate, *Scr* serum creatinine, *PT* prothrombin time, *APTT* activated partial thromboplastin time, *FIB* fibrinogen *ESRD* end-stage renal disease, *ALT* alanine transaminase, *AST* aspartate aminotransferase, *GGT* gamma-glutamyl transpeptidase, *TC* total cholesterol, *TGs* triglycerides, *LDL-C* low-density lipoprotein cholesterol, *HDL-C* high-density lipoprotein cholesterol, *TCM* traditional Chinese medicine

“×^*^” only for subjects that undergo losartan potassium unification (50 mg per day). “×^#^” only for subjects that take losartan potassium at 50 mg per day before enrollment

### Study settings and recruitment

Assuming a 20% dropout rate, a total of 252 patients will be recruited from the eighteen centers mentioned above using posters, the hospitals’ websites, and networks from December 2019 to December 2020. Research assistants will manage the recruitment, and endocrinologists will diagnose the participants. On the consent form, participants will be asked for permission to apply their data in case of withdrawal. Participants will also be asked to agree to share the research data with people from the hospitals participating in the study or from regulatory authorities where relevant. Biological specimens are not stored in this study. The trial adopted clinical trial insurance, and affected participants will receive appropriate coverage if serious harm occurs following the trial.

### Participants

Subjects will be deemed eligible participants if they meet all of the listed inclusion criteria and none of the listed exclusion criteria.

#### Inclusion criteria

Diagnoses of type 2 diabetes based on the American Diabetes Association (ADA) criteria [18] and DKD defined by *National Kidney Foundation Kidney Disease Outcomes Quality Initiative (NKF K-DOQI) guidelines* [19]. Participants who meet any of the following criteria can be considered as DKD: a, large amounts of albuminuria; b, diabetic retinopathy with chronic kidney disease at any stage; and c, microalbuminuria combined with a greater than 10-year course of type 1 diabetes.Diagnoses of TCM syndromes of qi and yin deficiency and blood stasis were constructed based on Diagnosis and Treatment of Diabetes and Its Complications with Integrated Chinese and Western Medicine as follows: Primary signs/symptoms include dry mouth and throat, and fatigue. Secondary signs/symptoms include a propensity to be hungry and eat more; shortness of breath; heat sensation in chest, palms, and soles; fixed pain in the chest, lower back, or limbs; and numbness of the limbs. Participants who suffered from the primary signs/symptoms and at least two of the secondary signs/symptoms combined with the tongue manifestation are considered to exhibit syndromes of qi and yin deficiency and blood stasis.A UACR ≥ 30 mg/g.An estimated glomerular filtration rate (eGFR, according to the Chronic Kidney Disease Epidemiology Collaboration (CKD-EPI) equation) ≥ 30 ml/min/1.73 m^2^ and ≤ 59 ml/min/1.73 m^2^.A fasting blood glucose level < 13.9 mmol/l and/or a 2-h postprandial blood glucose level < 16.6 mmol/l.A glycated hemoglobin (hemoglobin A1c, HbA1c) percentage ≤ 10%.An age between 35 and 75 years, male or female.Voluntary participation in this clinical study and provision of written informed consent.

#### Exclusion criteria

A diagnosis of type 1 diabetes.A lack of diagnosed diabetic retinopathy.A history of simple renal hematuria or proteinuria with hematuria, sudden onset of edema and mass proteinuria without abnormal renal function, significant renal tubular dysfunction, coexisting renal tubular abnormalities, primary glomerulonephritis or secondary nephritis except DKD, or acute or chronic infection of the urinary system.A hemoglobin (HGB) concentration < 90 g/l.An ALB concentration < 30 g/l.A diagnosis of renal artery stenosis.A serum potassium concentration > 5.5 mmol/l.A serum creatinine (Scr) concentration ≥ 3 mg/dl (256 μmol/l).A history of severe cardiovascular or cerebrovascular disease within 3 months before screening.Severe systemic primary disease or dysfunction.Severe liver dysfunction or ALT or AST levels higher than 2.5 times the normal range.Hypertension treated with more than 3 types of antihypertensive drugs, blood pressure that is poorly controlled after administration of drugs with systolic blood pressure (SBP) ≥ 140 mmHg or diastolic blood pressure (DBP) ≥ 90 mmHg, or hypotension with SBP ≤ 90 mmHg or DBP ≤ 60 mmHg (resting position).Chronic (for more than 3 weeks) or recurrent diarrhea (where diarrhea is defined as elimination of increased volumes of thin fecal matter with increased frequency (> 3 times/day)).A history of active bleeding in the 3 months before screening.Coagulation disorders.Drug allergies or allergies to KLX or the active ingredient in losartan potassium.A history of alcohol or drug abuse or psychiatric disorders.Pregnancy, lactation, or plans to become pregnant during the trial.A history of enrollment in other clinical studies in the past 3 months.Other circumstances under which the investigators considered it inappropriate to participate in this clinical study.

### Randomization, allocation concealment, and blinding

The participants will have an individual trial identification number and be randomly assigned to either the losartan potassium plus KLX group or the losartan potassium plus placebo group in a 1:1 ratio. Randomization will be performed using Statistics Analysis System (SAS) software by an independent statistical agency. The Data Management Center of Guang’anmen Hospital will be responsible for drug blinding and randomization concealment. The statistician will not participate in the randomization and will analyze the collected data without having access to allocation information. Research assistants will enroll patients at the 18 participating medical centers sequentially on the basis of screening order. Both the participants and the investigators will be kept blinded to the allocations until the trial is completed. In case of a severe adverse event, an administrator at the Data Management Center of Guang’anmen Hospital will unblind the patient information as an emergency measure and provide appropriate treatment.

### Intervention

All investigators will be trained before the start of the study according to an investigators’ brochure. The enrolled patients with DKD will be asked to take losartan potassium tablets (50 mg per day) as the basic treatment and will also be administered KLX or placebo. The subjects in the treatment group will take four capsules of KLX orally thrice a day for 24 weeks. The participants in the control group will take the same amount of placebo for 24 weeks. Data from all the participants will be collected in four periods: on day 0 (V2), at 4 weeks ± 3 days (V3), at 12 weeks ± 5 days (V4), and at 24 weeks ± 5 days (V5).

KLX consists of six natural herbs: *Astragalus membranaceus*, *Ligustrum lucidum*, leech, rhubarb, Radix Pseudostellariae, and the fruit of the Chinese wolfberry. The placebo is identical in appearance and properties to KLX capsule without any active ingredient. Both KLX and the placebo will be manufactured by Chengdu Kanghong Pharmaceutical Co., Ltd., at a dose of 500 mg. The placebo, which will be identical in appearance and properties to KLX, will contain no active ingredients. The placebo will be verified by the quality control department and will meet the standards of placebo preparation. The interventions should stop for a given participant if the creatinine doubles or ESRD is detected. The participants will be asked to refrain from taking any other treatment for diabetic nephropathy, including ACEI or ARB drugs other than losartan potassium tablets and calcium hydroxybenzenesulfonate as well as Chinese medicine that affect evaluation of qi and yin deficiency and blood stasis syndrome during the trial.

### Outcome measures

#### Primary outcomes

The primary endpoint is the decline in the eGFR (ml/min/1.73 m^2^/year).

#### Secondary outcomes

The secondary outcomes will include the incidence of Scr doubling, the incidence of ESRD, the proportion of subjects with a progressive decline in eGFR of > 30% from baseline, the percent change in 24-h UTP, the change in UACR from baseline, and the total effective rate of TCM syndrome scale scores at every visit and follow-up point, including the 4th, 12th, and 24th weeks as well as the 6th and 12th months.

#### Safety assessments

To assess the safety of KLX treatment in patients with DKD, vital signs and some laboratory parameters will be measured and electrocardiography will be performed during the intervention period of the trial. In detail, the vital signs will include body temperature, blood pressure, respiratory rate, and pulse rate. The biological indicators we will monitor will include routine blood indices (red blood cell count (RBCs), hemoglobin(HGB), white blood cell count (WBCs), and platelet count (PLTs)), routine urine and urine sediment parameters (assessed under microscopy), 24-h UTP levels, UACRs, liver function indices (alanine aminotransferase (ALT), aspartate aminotransferase (AST), alkaline phosphatase (ALP), total bilirubin (TBIL), and γ-glutamyl transferase (GGT)), renal function indices (eGFR and Scr), serum electrolytes (K^+^, Na^+^, and Cl^−^), blood lipid profile indices (total cholesterol (TC), triglycerides (TGs), high-density lipoprotein cholesterol (HDL-C), and low-density lipoprotein cholesterol (LDL-C)), coagulatory function indices (prothrombin time (PT), activated partial thromboplastin time (APTT), and fibrinogen (FIB)), HbA1c levels, and fasting blood glucose levels. To reduce risk, vital signs and some laboratory parameters of the participants will be monitored during the intervention period of the trial. Clinical experts will evaluate the participants’ condition at every visit. Moreover, detailed information about any adverse events will be recorded, including the severity, rate of incidence, and correlation with the treatment. Adverse events will be monitored and treated until properly resolved.

### Compliance

The investigators are responsible for informing and supervising the participants to take the products strictly according to regulations. The details about medication should be reported and recorded at every visit in the case report forms. Those with drug doses less than 80% or greater than 120% of the prescribed amount will be withdrawn from the trial and considered as noncompliance. Moreover, the specific withdrawal reasons should be recorded in CRFs as well.

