Full Analysis Set (FAS), Per Protocol Set (PPS), and Safety Set (SS) are to be used for data analysis. According to intention-to-treat principle, FAS is defined as analysis of all cases who met all the inclusion criteria and none of the exclusion criteria, were randomized, and had at least one dose of the study drug. It included all enrolled and dropout cases except excluding participants. Multiple imputation analysis will be carried to explain the effect of missing data. Missing data of the primary outcomes will be carried forward with the principle of the last observation carried forward (LOCF). PPS includes the data from the subjects who follow the test protocol strictly, have good compliance, do not take the prohibited drugs during the test period, and complete the CRF form. SS refers to the participants who have made at least one visit and actual data recorded for safety indicators.

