To evaluate the effect of KLX, data were analyzed primarily using an intention-to-treat principle, and per-protocol analysis served as a supplement. For the primary outcomes, we will calculate the changes of eGFR from baseline. To compare the decline in eGFR between two groups, repeated-measures analysis of covariance model will be performed using baseline eGFR as covariates. Least-square means with SEMs and two-sided 95% CIs for differences between groups were estimated. For secondary outcomes, statistical description and comparison between groups will be performed according to whether the variables are continuous or categorical data. To be specific, the difference in classification indicators among secondary outcomes, including the incidence of Scr doubling, the incidence of ESRD, and the proportion of subjects with a progressive decline in eGFR of > 30% from baseline within 24 weeks, between groups will be compared using chi-squared or Fisher’s exact test. While the difference in the total effective rate of TCM syndrome scale scores between the two groups will be tested as rank data using Wilcoxon’s test or CMH test. Comparison of the continuous variables, such as the percent change in 24-h UTP and the change in UACR, will be performed applying independent *t* tests (or the Mann-Whitney *U* test). Safety evaluation is composed of comparison of parameters listed above as well as adverse events evaluation. Besides the detailed description, reason, and explanation of the adverse events, the chi-squared test or Fisher’s exact test will be used to compare the incidence of AEs between the two groups.

There will be no interim analysis of the data because there are no anticipated problems that are detrimental to the participants. All the data will be analyzed using Statistical Package for the Social Sciences (SPSS) version 17.0 (SPSS, Inc., Chicago, IL) software. All statistical tests will be two-sided, and significance will be considered for *p* values < 0.05.

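### Withdrawing patients outside 80–120% of study drug from the trial, not only from the per-protocol set, may leave eGFR uncollected and undermines the primary intention-to-treat analysis

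*Protocol article*

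**What the plan says.** The Compliance section sets the rule: "Those with drug doses less than 80% or greater than 120% of the prescribed amount will be withdrawn from the trial". It also has medication use recorded at each visit and the reason for each withdrawal entered in the case report form. The Intervention section words a halt to treatment differently, for renal events: "The interventions should stop for a given participant if the creatinine doubles or ESRD is detected".

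Under Data analyses, "data were analyzed primarily using an intention-to-treat principle, and per-protocol analysis served as a supplement". Dropouts stay in the FAS: "It included all enrolled and dropout cases except excluding participants". Missing values are covered by two sentences. The first is general: "Multiple imputation analysis will be carried to explain the effect of missing data". The second concerns the primary outcome: "Missing data of the primary outcomes will be carried forward with the principle of the last observation carried forward (LOCF". Adherence already has a place in the analysis sets: "PPS includes the data from the subjects who follow the test protocol strictly, have good compliance".

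Post-baseline visits are at weeks 4 (V3), 12 (V4) and 24 (V5). The Secondary outcomes section adds time points at 6 and 12 months. The Follow-up section promises a re-assessment of everyone included at those two times, by telephone or in clinic.

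**The concern.** Adherence arises after randomisation, and treatment can affect it through tolerability, perceived benefit and the load of 12 capsules a day (four capsules, three times). If poor adherence ends participation, eGFR values that the primary analysis needs may never be measured. The patient is still counted as randomised, but the outcome is then a carried-forward value and not an observation.

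In a trial of declining eGFR, carrying a value forward freezes the decline at that point. If the arms lose similar shares, the treatment difference shrinks. If they lose different shares, the result can move either way. A larger sample does not remove this bias, and values that were never collected cannot be recovered at analysis. The rule gains nothing for the per-protocol analysis, which already requires good compliance.

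**Working it through.** **1. Is this only loose wording for stopping study drug?** The article has separate language for that. In the Intervention section the treatment stops; in the Compliance section the patient leaves the trial and a withdrawal reason is recorded. The plain reading is that participation ends.

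**2. Which eGFR values are at stake?** This depends on when the 80–120% threshold is applied, which the article does not say (per visit or cumulative).
- Applied at V3: weeks 12 and 24 are lost.
- Applied at V4: week 24 is lost.
- Applied only at V5: no value up to week 24 is lost.

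**3. The plan's own figures (Sample size).** Mean declines per half year are 1.38 (SD 3.21) with KLX and 2.61 (SD 3.16) with placebo.
- Difference = 2.61 − 1.38 = 1.23.
- Pooled SD = √[(3.21² + 3.16²)/2] = 3.185.
- The stated 105 per group for 90% power (two-sided 5%) is not reproduced. The normal formula gives 141 per group for 90% and 106 for 80%; power at 105 is 79.9%. That is a separate matter.
- The planned 126 per group equals 105 × 1.2. With all 126 per group observed, power is 86.5%, which is the reference below.

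**4. LOCF illustration.** Assumptions, not from the article: linear decline, SD unchanged, 126 per group, withdrawn share w, and last value at week 4 (f = 4/24 = 1/6 of the decline) or week 12 (f = 1/2). The mean decline in an arm becomes

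m × [1 − w × (1 − f)].

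*Equal withdrawal, planned declines:* difference = 1.23 × [1 − w(1 − f)].

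| w in both arms | Week 4 carried: difference (power) | Week 12 carried: difference (power) |
|---|---|---|
| 5% | 1.18 (83.6%) | 1.20 (84.8%) |
| 10% | 1.13 (80.2%) | 1.17 (82.9%) |
| 20% | 1.03 (72.4%) | 1.11 (78.8%) |

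*Unequal withdrawal, no true effect (both arms decline by 2.61), 20% KLX and 10% placebo:*
- Week 4: 2.61 × (0.20 − 0.10) × 5/6 = 0.22 in favour of KLX (18% of 1.23).
- Week 12: 2.61 × (0.20 − 0.10) × 1/2 = 0.13 in favour of KLX (11% of 1.23).

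*Unequal withdrawal, planned declines, week 4 carried:*
- 20% KLX, 10% placebo: KLX 1.38 × 0.833 = 1.15; placebo 2.61 × 0.917 = 2.39; difference 1.24, a shift of about +0.01.
- 10% KLX, 20% placebo: KLX 1.38 × 0.917 = 1.265; placebo 2.61 × 0.833 = 2.175; difference 0.91, a shift of 0.32 against KLX.

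**5. Does the later follow-up fill the gap?** The Follow-up section does not say that withdrawn patients are included. It also allows telephone contact, which cannot give an eGFR. Yet the Secondary outcomes section lists creatinine doubling and eGFR decline of more than 30% at 6 and 12 months, and both need laboratory values. These sections and the Compliance section do not fit together as written.

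**The case against.** The strongest defence is that the plan limits the damage. Collected data are kept, dropouts stay in the FAS, and the consent form asks permission to use data after withdrawal (Study settings and recruitment). Multiple imputation is named alongside LOCF, and the Follow-up section can be read as covering everyone. A condensed article may also omit when adherence is judged.

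Much of this stands, and it rules out several stronger readings that a reader might infer:
- *That the rule deletes data or removes these patients from the intention-to-treat population.* The FAS wording keeps dropouts, so the analysis is weakened, not abolished.
- *That the week 12 and week 24 values are always lost.* That needs withdrawal at V3, and the timing is not stated.
- *That these losses add to the planned 20%*, for example 126 × 0.8 × 0.9 = 90.7 per arm at an assumed 10%. The Sample size section itself calls its 20% a withdrawal rate, so these patients most naturally fall within it.
- *That the rule favours KLX.* With equal losses it shrinks the difference. With unequal losses the direction depends on which arm loses more patients and on the true effect.

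The core is untouched. The sentence sends non-adherent patients out of the trial, and nothing in the article clearly secures their later eGFR. Multiple imputation does not cure this. If non-adherent patients are withdrawn, few or no observed outcomes after non-adherence remain to impute from, and the sentence on the primary outcome names LOCF. Part of the numerical harm does belong to LOCF and not to the withdrawal rule, but it is the rule that creates the gaps.

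**Conclusion.** The concern holds in this form: the Compliance rule ends trial participation on a post-randomisation event, so scheduled eGFR may go uncollected and be carried forward, which undermines the primary intention-to-treat analysis. That the conflict exists follows from the text. Its size does not, because neither the share of patients outside 80–120% nor the timing of withdrawal is given.

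Under the stated assumptions, equal withdrawal of 5–20% reduces the planned 1.23 to between 1.20 and 1.03, and power from 86.5% to between 84.8% and 72.4%. A 10-point imbalance gives anything from a false benefit of 0.22 to a loss of 0.32 for KLX. These are scenarios, not predictions. Because the primary endpoint is affected and unmeasured values cannot be restored later, the rule should be changed while patients are still in follow-up.

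**What to change.** In the Compliance section, replace withdrawal from the trial with this rule: adherence outside 80–120% is recorded as a protocol deviation and excludes the patient from the PPS only; the patient stays in follow-up, has eGFR measured at all remaining scheduled visits, and is analysed in the FAS as randomised. State that whether study drug continues is a separate clinical decision.

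Reconcile the Secondary outcomes and Follow-up sections with this rule. Say whether patients who stop or deviate are included at 6 and 12 months, and that outcomes based on creatinine or eGFR need a laboratory sample and not only a call. State when adherence is judged.

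The cost is a small protocol amendment, for which the Protocol amendments section gives a route, plus completion of visits already on the schedule for the patients retained.
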